### Pre-planned primary analysis

The statistical analysis will be carried out under the current recommendations for non-inferiority trial analysis [23].

The analysis of the primary outcome will be undertaken on the intention to treat principle including all randomized patients, and under the “per-protocol” principle, including all randomly assigned patients except those who withdrew consent for the use of all trial data, those who did not meet the inclusion criteria, those who did not receive the allocated study treatment, and those without data for the primary outcome [22, 23]. To comply with international recommendations on non-inferiority trials [24], the analysis based on the intention-to-treat principle and the data set for the per-protocol analysis will have equal importance to lead similar to a robust interpretation.

For the primary endpoint (proportion of successful tracheal intubation without major complications), the proportion difference between the two groups and the two-sided 95% confidence interval will be estimated. Under our assumptions, the remifentanil group will be considered non-inferior if the upper limit of the two-sided 95% confidence interval of absolute proportion difference does not exceed 7% (non-inferiority margin). The confidence interval will be estimated by a logistic model considering stratification on the existence or not of an occlusive syndrome and the type of equipment used for intubation. As the primary endpoint is identified within 10 min of anesthetic induction and death is included in the endpoint, a small amount of missing data will be expected. Multiple imputations methods based on demographic criteria and available data will be used in case of missing data. If non-inferiority is shown for the primary endpoint (on “intention-to-treat” and “per-protocol” populations), a superiority test will be assessed.

Preplanned subgroup analyses will be carried out on the primary outcome, following the same methodology:
Randomization stratum
*Type of equipment used for intubation (Macintosh laryngoscope vs. video laryngoscope).*Primary risk factor for pulmonary aspiration of gastric contents (occlusive syndrome vs. other causes)Age groups (18–40 years; 40–60 years; 60–80 years)Mallampati score (I and II vs. III and IV)Standard of care (urgent or non-urgent)Body mass index greater than 30 kg/m^2^ (yes vs. no)ASA Score (1–2 vs. 3–4)Choice of propofol as hypnotic (propofol vs. others)

For secondary endpoints, the two groups will be compared with the use of logistic regression models for binary data (postoperative pneumonia, postoperative respiratory distress), with the use of linear regression models for continuous data (heart rate, systolic blood pressure) and with the use of Poisson regression models for count data (number of episodes of allergic manifestation, number of episodes of desaturation). All analyses will be adjusted for stratification factors and centers as random effect.

Continuous variables will be presented as mean and S.D.s (as median and quartiles, otherwise). Categorical data will be presented as exact numbers and percentages.

The DSMB will periodically conduct safety analyses, as described in the “Study oversight” section.

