## Methods

### Study population

Patients, aged from 18 to 80 years old, seen by investigators in planned anesthesia consultations or during their admission to the operating room and who will have a surgical or interventional procedure under general anesthesia with tracheal intubation and considered at risk of pulmonary aspiration of gastric contents may be offered to participate to the study. The risk of pulmonary aspiration of gastric contents was defined by at least one of the following criteria: pre-operative fasting period less than 6 h, occlusive syndrome, functional ileus, vomiting episode within the last 12 h, orthopedic trauma within the last 12 h, medical history of symptomatic gastroesophageal reflux or hiatus hernia or gastroparesis or dysautonomia or gastroesophageal surgery with sphincter dysfunction.

Patients who met any of the following criteria will be excluded from the study: pregnant women, contraindication to any rapid-onset paralytic agent (known allergy to rapid muscle relaxant drugs, personal or family history of known malignant hyperthermia, congenital muscular dystrophy, myasthenia, a known congenital deficit in plasma pseudocholinesterase), intended use of etomidate as hypnotic to induce anesthesia, prediction of impossible tracheal intubation, pre-operative respiratory failure (SpO_2_ < 95%), pre-operative hemodynamic failure (mean arterial pressure under 65 mmHg or use of vasopressor), patient in cardiac arrest, patient under justice protection, and the absence of affiliation with French social security system.

The modalities for obtaining patient consent by Investigating Physicians are described in the “Ethics” section.

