### Protocol drop-out

Patients not receiving the attributed drugs or receiving the other study drug as rescue therapy for non-predicted difficult intubation will be kept in analysis and remain analyzed with their randomized group.

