### Sample size

The proportion of successful tracheal intubation without any major complications is the primary outcome. In previous studies, the proportion of rapid sequence induction of general anesthesia with a rapid-onset paralytic agent without major complications ranged between 70 and 92%, depending on the studies and definitions [19–21]. It is also recommended to set non-inferiority margins lower than a 10% relative difference between the intervention and control groups [22]. Assuming an 80% rate of tracheal intubation without major complication in the rapid-onset paralytic agent group, and given the potential benefit of avoiding the use of rapid paralytic agents, we deemed it medically acceptable to set the non-inferiority margin to an absolute difference of 7% (8.75% relative difference). We thus calculated that a total of 1150 patients (575 patients per group) was needed to demonstrate the non-inferiority of the intervention with a statistical power of 80% an alpha risk of 2.5.

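### The primary model names only the two randomization strata in both analysis sets; adding baseline covariates already collected would be a nearly free improvement, chiefly for the per-protocol set

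*Protocol article*

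**What the plan says.** Under *Pre-planned primary analysis*, the model is described thus: "The confidence interval will be estimated by a logistic model considering stratification on the existence or not of an occlusive syndrome", and the equipment type is added as the second stratum. One model is given for both the intention-to-treat and the per-protocol set, and the two sets are declared equally important. The per-protocol set leaves out, among others, "those who did not receive the allocated study treatment". The following paragraph, on secondary endpoints, closes with a sentence that adjusts all analyses for the strata and for centre as a random effect. It is unclear whether that reaches the primary model.

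Other baseline variables appear elsewhere. Age, BMI, ASA, urgency and "Mallampati score (I and II vs. III and IV") are subgroup factors in the same section. *Study population* excludes patients with SpO2 below 95%, and those with "mean arterial pressure under 65 mmHg or use of vasopressor", so both measurements must be checked before entry. *Masking protocol* says that local investigators cannot be blinded. *Protocol drop-out* covers "Patients not receiving the attributed drugs" and those given the other drug as rescue, and keeps both in their randomized group.

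**The concern.** The composite endpoint includes first-attempt failure, desaturation below 95% and extreme MAP. Airway grade, BMI, age, ASA class, urgency and pre-operative SpO2 and MAP are plausible predictors of those components. The plan already counts on such information for imputing missing outcomes, which is to use demographic and other available data, yet the estimating model does not use it.

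Two things are at stake. In the intention-to-treat set, some precision is left unused on the confidence limit that decides non-inferiority. In the per-protocol set the issue is bias. Whether a patient receives the allocated drug is decided by a clinician who knows the allocation and can see the airway. If harder airways drop out of one arm more than the other, the sets being compared are no longer randomized, and a model holding only occlusive syndrome and device cannot restore balance on the other factors.

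**Working it through.** **Inputs from the article (*Sample size*).** "Assuming an 80% rate of tracheal intubation without major complication in the rapid-onset paralytic agent group"; "we deemed it medically acceptable to set the non-inferiority margin to an absolute difference of 7% (8.75% relative difference"); "a total of 1150 patients (575 patients per group) was needed to demonstrate the non-inferiority"; power 80%, alpha 2.5 (read as one-sided 2.5%).

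**1. The plan's own figure.** Comparing 80% with 73%, pooled rate 0.765:

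n = [1.96 × √(2 × 0.765 × 0.235) + 0.8416 × √(0.80 × 0.20 + 0.73 × 0.27)]² / 0.07² = (1.1753 + 0.5029)² / 0.0049 ≈ 574.8, so 575 per group. The stated size is reproduced with no covariate gain assumed.

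**2. Precision in the intention-to-treat set.** With 80% success in both arms, SE = √(0.32 × (1 − R²) / 575), half-width = 1.96 × SE and power = Φ(0.07/SE − 1.96). R² is the share of outcome variance removed by the added covariates. The article does not give it, so it is an assumption.

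| R² | SE (points) | Half-width (points) | Power |
|---|---|---|---|
| 0% | 2.36 | 4.62 | 84.3% |
| 5% | 2.30 | 4.51 | 86.1% |
| 10% | 2.24 | 4.39 | 87.9% |
| 14% | 2.19 | 4.29 | 89.2% |

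As a guide to what R² might be, a combined risk score with an odds ratio of 1.5, 2.0 or 2.5 per SD gives R² of about 2.6%, 7.1% or 11.6%, and half-widths of 4.56, 4.46 or 4.35 points. The gain is real but modest. With 518 per arm (10% lost, assumption) and no covariates, power is still 80.4%.

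**3. Shift in the per-protocol set.** Take a high-risk class with share p and a success rate lower by g points. In the remifentanil arm only, a fraction h of the high-risk and l of the other patients do not receive the allocated drug and are removed. The share left is p′ = p(1−h) / [p(1−h) + (1−p)(1−l)], and the shift is (p − p′) × g towards non-inferiority. All of p, g, h and l are assumptions.

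| p | g | h / l | p′ | Shift (points) |
|---|---|---|---|---|
| 30% | 14.3 | 5% / 1% | 0.285/0.978 = 29.1% | 0.12 |
| 15% | 17.5 | 20% / 2% | 0.120/0.953 = 12.6% | 0.42 |
| 15% | 17.5 | 40% / 2% | 0.090/0.923 = 9.8% | 0.92 |
| 20% | 20 | 30% / 2% | 0.140/0.924 = 15.2% | 0.97 |
| 30% | 28.6 | 20% / 3% | 0.240/0.919 = 26.1% | 1.11 |
| 20% | 20 | 40% / 2% | 0.120/0.904 = 13.3% | 1.345 |

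The range is thus roughly 0.1 to 1.3 points, that is 2% to 19% of the 7-point margin (0.12/7 and 1.345/7). The direction follows from placing the non-receipt in the remifentanil arm; in the control arm it would reverse.

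**4. Error in the per-protocol set taken alone.** At a true 7-point deficit the SE is √((0.16 + 0.1971)/575) = 2.49 points, or about 2.5 once a few patients are removed. Φ(shift/SE − 1.96) gives about 3.7% for a shift of 0.42 and about 5.7% for 0.97, against the nominal 2.5%.

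**The case against.** The best defence is that adjusting for the stratification factors is a valid analysis. The strata are also the only variables that the article itself calls risk factors (*Treatment allocation*). The trial meets its stated power without further covariates, the article condenses a fuller plan, and nothing in it forbids adding terms. All of this stands, and it is why the point is an improvement and not an error.

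Several stronger readings are tempting, and the documents do not support them:

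- **That the intention-to-treat result is biased or underpowered.** Randomization protects it, and power at no true difference is about 84% against a stated 80%.
- **That the omitted variables are strong predictors.** No passage says so. Listing a variable as a subgroup factor does not show prognostic strength.
- **That the model certainly holds the two strata and nothing else.** The closing sentence on adjustment may add centre to it, though centre would not stand in for individual airway or physiological risk.
- **That the trial's false-claim rate is 3.7% to 5.7%.** Those rates are for the per-protocol set alone. If both sets must pass, the joint rate cannot exceed the intention-to-treat rate, which is 2.5% when the intention-to-treat difference lies at the margin. One limit on that comfort: if remifentanil-arm non-receivers do as well as controls, the intention-to-treat deficit is diluted too, for example 7 × (1 − 0.047) = 6.67 points.
- **That every drug switch leaves the per-protocol set.** The exclusion is for not receiving the allocated drug. A patient who received it and was then given the other drug as rescue is not clearly excluded.
- **That no new data are ever needed.** The eligibility checks on SpO2 and MAP do not show that numeric values reach the case report form, and recording of pre-induction heart rate is not mentioned.

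**Conclusion.** The point holds as a recommended improvement. The article fixes a primary model that names only the two strata for two equally weighted sets and leaves plausibly prognostic collected variables unused. In the intention-to-treat set the benefit is about 0.1 to 0.3 points of half-width and 2 to 5 percentage points of power, if R² is 5% to 14%. In the per-protocol set the possible confounding is roughly 0.1 to 1.3 points, given the assumed risk classes and one-sided non-receipt. No figure in the article supports or excludes those rates. Adjustment would remove only the part of that confounding carried by measured factors. The per-protocol argument is the better reason to act, because there the adjustment addresses bias and not just precision.

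**What to change.** In *Pre-planned primary analysis*, before unblinding:

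- State that the logistic model for both sets includes the two strata plus age and BMI (continuous), Mallampati, ASA and urgency. Add pre-operative SpO2 and MAP if their numeric values are recorded.
- Obtain the absolute difference and its interval by standardization from that model. This keeps the absolute-difference estimand and the 7-point margin.
- Leave out anything chosen after allocation. The hypnotic is at the physician's discretion with no stated timing, so it is not a safe baseline covariate.
- Keep the strata-only model as a sensitivity analysis.
- State whether the centre random effect applies to the primary model.

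For the continuous secondary outcomes, add the pre-induction value of the same measurement where it is recorded.

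The cost is wording, plus simple imputation of a few missing baseline values. No extra patients are needed, and no new data for the five subgroup variables. The article says the data analysts are blinded and planned recruitment to October 2021, so there was time to pre-specify this.

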### Masking protocol

It is not possible to blind local investigators to allocation as it is obvious clinically which patients are receiving rapid-onset paralytic agents. Patients are blinded to the group allocation as well as the data analysts.

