### Procedures

The choice of hypnotics is at the physician’s discretion with dosage based on estimated patient weight and height. The injection of the hypnotic is followed immediately by an intravenous bolus of either remifentanil (3 to 4 μg/kg) in the intervention group or rapid-onset paralytic agent (1 mg/kg of succinylcholine or 1 mg/kg of rocuronium at the physician’s discretion) in the control group, with weight adjustment according to the body mass index (Supplemental Table S2). It is recommended to perform the tracheal intubation 30 to 60 s after administering the paralytic agent or the remifentanil. In the rapid-onset paralytic agent group, no opioid is injected before the tracheal intubation. In case of difficult unplanned intubation, the physicians are free to use a rapid-onset paralytic agent or remifentanil as rescue therapies (Fig. 2).

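### The subgroup analyses inherit the primary non-inferiority method, which invites underpowered verdicts against 7 points instead of asking whether the effect varies, and the hypnotic subgroup is not tied to a pre-randomization choice

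*Protocol article*

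**What the plan says.** All references are to the protocol article.

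- **Primary rule.** Under Pre-planned primary analysis, remifentanil is declared "non-inferior if the upper limit of the two-sided 95% confidence interval of absolute proportion difference does not exceed 7" per cent. The interval comes from a logistic model that takes account of the two stratification factors.
- **Subgroups.** The same section continues: "Preplanned subgroup analyses will be carried out on the primary outcome, following the same methodology". It then lists eight factors: laryngoscope type, occlusive syndrome, age, Mallampati score, urgency, body mass index, ASA score and hypnotic. The last is worded "Choice of propofol as hypnotic (propofol vs. others"). It mentions no comparison of the effect between levels.
- **Hypnotic.** Under Procedures, "The choice of hypnotics is at the physician’s discretion". Nothing is said about when the choice is made relative to randomization.
- **Laryngoscope, for contrast.** Standard care also leaves this to the physician, but requires it to be settled before randomization.
- **Blinding.** Under Masking protocol, "It is not possible to blind local investigators to allocation".
- **Age bands.** These are 18–40, 40–60 and 60–80 years, so ages 40 and 60 each fall in two bands.

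**The concern.** A subgroup analysis should ask whether the treatment effect differs between levels. Judging each level separately against the margin asks whether that level alone has enough patients to exclude a 7-point loss. The trial was sized to answer that once, with all 1150 patients. Small levels will often miss the margin with no difference in effect at all, and a reader could take this as evidence that remifentanil does worse in those patients.

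The hypnotic subgroup raises a different issue. A subgroup comparison keeps the protection of randomization only if membership cannot depend on the allocated arm. The other seven factors are patient or procedure characteristics, or are fixed beforehand. The hypnotic is a choice by an unblinded physician with no stated time limit. If allocation influences the choice, propofol patients in the two arms need not be comparable.

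**Working it through.** **Inputs**

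- Control success rate 80%: "Assuming an 80% rate of tracheal intubation without major complication in the rapid-onset paralytic agent group" (Sample size).
- Margin: "set the non-inferiority margin to an absolute difference of 7% (8.75% relative difference") (Sample size).
- 575 patients per group, 80% power and an alpha of 2.5, read as one-sided 2.5% to match the two-sided 95% interval.
- True difference: not given. The section says only that the number is "needed to demonstrate the non-inferiority of the intervention". I assume 0 and vary it to 2 and 5 points in favour of remifentanil.
- Subgroup shares: not given. I use 10% to 90%.

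**Step 1: the plan's own figure.** The two-proportion formula with pooled variance under the null, 80% against 73%, two-sided 5%, power 80%, gives

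n = [1.96·√(2·0.765·0.235) + 0.842·√(0.16 + 0.1971)]² / 0.07² ≈ 575 per group.

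This reproduces 575 and 1150 exactly. The usual non-inferiority formula with 80% in both arms gives (1.96 + 0.842)²·0.32/0.07² ≈ 513 per group. With 575 per group, power at a true difference of 0 is therefore 84.3%. The trial as a whole is not too small, and the issue is confined to the subgroups.

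**Step 2: chance that one level meets the margin.** Take the difference as control minus remifentanil, and let f be the level's share, so n = 575f per arm. At a true difference of 0,

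P(meets) = Φ(0.07/√(0.32/n) − 1.96).

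For f = 0.5: √(0.32/287.5) = 0.0334; 0.07/0.0334 − 1.96 ≈ 0.14; Φ ≈ 0.555.

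| Share | n per arm | 95% half-width (points) | Meets, true diff. 0 | Misses, true diff. 0 | Misses, remifentanil +2 | Misses, remifentanil +5 |
|---|---|---|---|---|---|---|
| 100% | 575 | 4.6 | 84.3% | 15.7% | 2.7% | <0.1% |
| 90% | 518 | 4.9 | 80.4% | 19.6% | 4.2% | 0.1% |
| 70% | 402 | 5.5 | 69.9% | 30.1% | 9.8% | 0.6% |
| 50% | 288 | 6.5 | 55.5% | 44.5% | 21.4% | 3.3% |
| 33% | 192 | 8.0 | 40.3% | 59.7% | 38.7% | 12.7% |
| 20% | 115 | 10.3 | 26.3% | 73.7% | 58.7% | 33.0% |
| 10% | 58 | 14.6 | 15.3% | 84.7% | 76.7% | 60.4% |

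The half-width reaches 7 points at n = 0.32·(1.96/0.07)² ≈ 251 per arm, a share of 251/575 ≈ 44%. Below that, a level with an observed difference of exactly zero and 80% success still misses the margin.

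**Step 3: how many levels miss.** Seven two-level factors and three age bands give 7·2 + 3 = 17 levels. With equal splits and a true difference of 0, the expected number missing is 14·0.445 + 3·0.597 ≈ 8.0.

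Simulation (4000 trials per scenario, constant effect, independent factors, unadjusted Wald interval) restricts this to trials that are non-inferior overall. The ranges run from equal splits to mostly 85/15 splits.

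| True difference | Mean levels missing, of 17 | At least 1 | At least 3 |
|---|---|---|---|
| 0 | 6.7 to 7.7 | 96% to >99.9% | 83% to 99% |
| Remifentanil +2 points | 3.8 to 6.0 | 83% to 99.7% | 54% to 94% |
| Remifentanil +5 points | 0.9 to 3.6 | 40% to 96% | 10% to 69% |

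**Step 4: the hypnotic.** No arithmetic applies. Standard care fixes the laryngoscope before randomization, Procedures sets no such requirement for the hypnotic, and Masking protocol leaves the physician unblinded. Study population excludes patients for whom etomidate is intended, so some intention exists at eligibility, but the text does not say that it is recorded or used to define the subgroup.

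**The case against.** Four points can be made on the other side.

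1. **The sentence may refer only to estimation**, meaning the model, the difference and its interval. The margin is not restated for subgroups, and no sentence says that each level will be declared non-inferior or not. This has some weight: a reader might infer that verdicts per level are certain, and the text does not go that far. Still, the decision rule is part of the only method described for the primary outcome, so carrying it over is the natural reading.
2. **Interaction tests and an exploratory label are usually left to the analysis plan.** Their absence alone would be no finding. Here, however, the article states a method, and a better analysis plan would have to depart from it.
3. **It is tempting to say that subgroups will fail, or that no level is large enough.** Neither is supported. The shares are unknown, a level holding 90% of patients keeps about 80% power, and with a true benefit of 5 points and equal splits the mean number missing is below one.
4. **It is tempting to say that the hypnotic is chosen after open-label allocation.** The document does not say so. The timing is left open, and the etomidate exclusion shows that the agent is considered at eligibility. Nor does the document state how the hypnotic acts on the blood-pressure components of the endpoint. What stands is that nothing prevents allocation from influencing the choice.

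It is also true that the subgroups do not touch the primary decision or the sample size.

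**Conclusion.** The point holds in a limited form. On its natural reading, the subgroup sentence applies a margin test at each level and does not examine whether effects differ. With a true difference near zero and 80% success in both arms, the chance of missing the margin is about 45% at half the patients, 60% at one third and 85% at one tenth. Several of 17 levels would then be expected to miss in a trial that succeeds overall. These figures rest on assumed shares, independent factors, a constant effect and an unadjusted interval, and they fall markedly if remifentanil is truly better.

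The hypnotic subgroup may be influenced by allocation because nothing fixes the choice beforehand; the document does not show that it is so influenced. The shared age limits are a minor slip. The primary conclusion is unaffected throughout.

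**What to change.** - **Subgroup method.** Replace the reference to the primary methodology by: the absolute difference with its 95% confidence interval for each level, a treatment-by-subgroup interaction test for each factor labelled exploratory, and no non-inferiority verdict per subgroup.
- **Hypnotic.** Define this subgroup by the agent intended before randomization where that is recorded, adding one field to the randomization form for remaining patients. For patients without it, label the analysis as not protected by randomization.
- **Age.** Make the bands disjoint, for example 18–39, 40–59 and 60–80.

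The cost is a change of wording and one form field; the sample size and primary analysis stay as they are. The downside is the low power of interaction tests, which should be stated. For a 50/50 factor, the standard error of the difference between two level-specific differences is √(2·0.32/287.5) ≈ 4.7 points, so 80% power needs a gap of about 2.80·4.7 ≈ 13 points. A non-significant interaction is therefore not evidence that the effect is uniform.

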### Standard care

Anesthesiologists are asked to follow the French guidelines for sedation and analgesia in the operating room. A trained anesthesiologist performs the tracheal intubation (> 4 semesters of training in anesthesiology for residents) or nurses specialized in anesthesiology (> 2 years of practice). In both groups, sedation induction is performed after preoxygenation (target FeO_2_ > 80%). The choice of laryngoscopes’ device (single-use Macintosh metallic laryngoscope blades (size 3 or 4) or video laryngoscopy) is at the physician’s discretion defined before randomization (criteria of stratification of the randomization). The uses of alternative airway procedures (for instance, stylet, backward, upwards, and rightwards pressure “BURP” maneuver or Sellick maneuver) are allowed. In case of major and minor complications associated with the study intervention, general anesthesia, or surgical procedure, post-trial care will comply with national and local protocols as appropriate. Especially in case of first intubation failure, an alternative procedure including the use of video laryngoscopy, gum elastic bougie, intubating laryngeal mask airway, or trans-cricothyroid oxygenation technique is recommended under the French guidelines on difficult airway management [15]. Hypotension is managed via fluid resuscitation with crystalloids and ephedrine, and prolonged hypotension is treated with continuous intravenous catecholamine administration [16].

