### Study endpoints

The primary endpoint is the proportion of patients with successful tracheal intubation without any significant complications up to 10 min after induction of anesthesia. Major complications during the first 10 min after induction of anesthesia are defined as the failure of tracheal intubation at the first attempt, pulmonary aspiration of gastric contents, oxygen desaturation < 95%, severe hemodynamic instability (mean arterial pressure (MAP) ≤ 50 mmHg or ≥ 110 mmHg for more than 3 min), severe arrhythmia (i.e., requiring pharmacological or electrical intervention or lasting more than 30 s), ventricular fibrillation or cardiac arrest, and anaphylactic reaction grade III or IV in HAS classification.

Secondary endpoints which will be compared between the two study groups are as follows:

In the operating theater: median intubation quality score (IDS-3 score) values [17], Cormack-Lehane (Supplemental Figure S1) and median POGO score values [18], percentage of patients requiring tracheal intubation alternative technique, median time between the administration of the hypnotic (start of anesthetic induction) and tracheal intubation (defined as the 6th capnography curve), median minimal value of SpO_2_ value within the first 10 min after anesthesia induction, percentage of patients with moderate desaturation (SpO_2_ ≤ 95%) or severe (SpO_2_ < 80%) within the first 10 min after anesthesia induction, percentage of patients with a severe hemodynamic disorder within the first 10 min after anesthesia induction (heart rate lower than 45 beats per minute (bpm) and/or higher than 110 bpm and/or a systolic blood pressure (SBP) lower than 80 mmHg and/or a SBP higher than 160 mmHg and/or a MAP of less than 55 mmHg and/or a MAP higher than 100 mmHg), frequency of patient with dental or tracheal injury during general anesthesia, frequency of patients with an allergic event of HAS 2013 grade I or II during general anesthesia, and the median doses of vasopressors used after induction,

In the recovery room: postoperative Sore Throat Score median values [19], percentage of patients with nausea, vomiting, aspiration of gastric contents, percentage of patients with laryngeal dyspnea, percentage of patients with SpO_2_ ≤ 92, percentage of patients with SpO_2_ < 80%, percentage of patients requiring post-extubation respiratory support, proportion of reintubation, and proportion of postoperative emergency ICU admission.

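### The linear models for heart rate and systolic blood pressure leave out the patient's pre-induction value: valid and unbiased, but less precise than they could be, and on secondary outcomes only

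*Protocol article*

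**What the plan says.** The text on secondary endpoints closes the section "Pre-planned primary analysis" of the protocol article. It assigns logistic models to binary data and Poisson models to counts. Continuous outcomes are to be compared "with the use of linear regression models for continuous data (heart rate, systolic blood pressure" being the two measures named. The covariates follow in one sentence: "All analyses will be adjusted for stratification factors and centers as random effect". Under "Treatment allocation" the stratification factors are the type of laryngoscopy and the presence of an occlusive syndrome. No pre-induction measurement is listed.

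Two related measurements are needed before inclusion. "Study population" excludes patients with "pre-operative hemodynamic failure (mean arterial pressure under 65 mmHg or use of vasopressor" among its criteria, and likewise "pre-operative respiratory failure (SpO_2_ < 95" percent. The article does not say whether pre-induction heart rate or systolic pressure is recorded.

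In "Study endpoints", the haemodynamic item is binary, the "percentage of patients with a severe hemodynamic disorder within the first 10 min after anesthesia induction", built from thresholds on heart rate, systolic pressure and mean pressure. Oxygenation has a continuous item, the "median minimal value of SpO_2_ value within the first 10 min after anesthesia induction".

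**The concern.** Heart rate and systolic pressure after induction are repeat readings of quantities that exist before it. The trial takes patients from 18 to 80 years, urgent and non-urgent, ASA 1 to 4, so starting values will vary widely. Laryngoscope type and occlusive syndrome can explain only part of that spread. Whatever they and centre do not explain stays in the residual and widens the interval for the treatment difference.

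The comparison is of interest: the Introduction cites fewer haemodynamic reactions with remifentanil in scheduled surgery, and the control group receives no opioid before intubation. What is at stake is the precision of that secondary comparison. In addition, if the arms happen to differ at baseline, a later decision to adjust would be post hoc.

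**Working it through.** **Inputs from the protocol article.** 575 per group and 1150 in total, 1:1 allocation, 80% success in the control group, 7-point margin, 80% power, and alpha of 2.5 (read as 2.5% one-sided).

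**Assumed input.** The correlation ρ between the pre-induction value and the outcome, within arm, strata and centre. The article gives none, so the range 0.1 to 0.7 is shown. SDs are taken as equal before and after induction.

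**The plan's own figure.** The only stated size is for the primary endpoint. Comparing 0.80 with 0.73 using a pooled variance (mean 0.765) and no continuity correction:

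n = [1.96·√(2·0.765·0.235) + 0.8416·√(0.80·0.20 + 0.73·0.27)]² / 0.07² = (1.175 + 0.503)² / 0.0049 ≈ 574.7, so 575 per group and 1150 in total.

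This matches. It concerns a binary endpoint and does not depend on the point made here.

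**Precision of the linear models.**
- Standard error of the difference without baseline: √(2/575) = 0.0590 SD.
- Detectable difference, two-sided 5%, 80% power: (1.96 + 0.8416) × 0.0590 = 0.165 SD.
- With the baseline value as covariate, the residual variance is multiplied by 1 − ρ², and the interval width and detectable difference by √(1 − ρ²). The equivalent unadjusted total is 1150 / (1 − ρ²).

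**Chance imbalance.** The 95% limit for the baseline difference between arms is 1.96 × 0.0590 = 0.116 SD. An imbalance of that size moves the unadjusted estimate by ρ × 0.116 SD.

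| ρ (assumed) | 1 − ρ² | Width factor | Detectable difference (SD) | Equivalent total N | Shift at 95% limit (SD) |
|---|---|---|---|---|---|
| 0.1 | 0.99 | 0.995 | 0.164 | 1162 | 0.012 |
| 0.3 | 0.91 | 0.954 | 0.158 | 1264 | 0.035 |
| 0.5 | 0.75 | 0.866 | 0.143 | 1533 | 0.058 |
| 0.7 | 0.51 | 0.714 | 0.118 | 2255 | 0.081 |

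**In mmHg, for illustration.** If systolic pressure had an SD of 20 mmHg (an assumption), the baseline imbalance limit would be 1.96 × 20 × √(2/575) = 2.3 mmHg. The part that reaches the estimate would be 0.1 × 2.3 = 0.2 mmHg up to 0.7 × 2.3 = 1.6 mmHg.

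**The case against.** The strongest reply is that this is an optional refinement of secondary analyses in a condensed article whose analysis plan is not shown. Further covariates are often named in such a plan, and adjusting for strata and centre is a standard choice. That lowers the weight but does not remove the point: the article does not stay silent, it names an adjustment set and applies it to all analyses.

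Other parts of the reply stand:
- **No continuous heart rate or systolic pressure item appears in the endpoint list.** Both occur only as examples in the analysis text, without a time point or summary, so the figures above apply to whatever is eventually modelled.
- **Availability is partly inferred.** Eligibility establishes pre-operative mean pressure and SpO2. That the same monitoring yields heart rate and systolic pressure is plausible but not stated, and a reading at a planned consultation is not the last one before induction.
- **The size is assumed.** Drug effects and vasopressor treatment after induction could weaken the correlation. At 0.1 the gain is negligible.

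A reader might also infer more than the documents support:
- **That the treatment effect is biased.** Randomisation keeps the unadjusted estimate unbiased and the type I error valid, and the interval already allows for chance imbalance.
- **That minimal SpO2 suffers equally.** The sentence on linear models does not name it. Baseline cannot lie below 95%, and "sedation induction is performed after preoxygenation (target FeO_2_ > 80" percent, so pre-induction SpO2 probably sits near its ceiling. With an assumed correlation of 0.1 to 0.3 the interval would be 0.5% to 5% narrower.
- **That the logistic model for the binary haemodynamic endpoint needs the same covariates.** The 1 − ρ² result is for linear models. In logistic regression, adjustment changes the odds ratio being estimated and generally does not shrink its standard error. That endpoint also counts both low and high values, so a linear baseline term could fit badly.

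**Conclusion.** The point holds as a minor matter of efficiency for heart rate and systolic blood pressure when they are modelled linearly. The stated adjustment set omits a prognostic variable. Under assumed correlations of 0.1 to 0.7 this leaves confidence intervals that could be about 0.5% to 29% narrower, and an unlucky baseline imbalance at its 95% limit would shift the estimate by about 0.01 to 0.08 SD. Where in that range the trial falls cannot be settled from the article, which gives neither a correlation nor an SD. The planned analysis is valid as it stands, no conclusion is shown to change, and the primary endpoint and its sample size are unaffected.

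**What to change.** In the secondary-endpoint text of "Pre-planned primary analysis", add one sentence: the linear models for heart rate and systolic blood pressure also include the pre-induction value of the same measure as a covariate. Where baseline systolic pressure is not recorded, use the pre-operative mean arterial pressure already assessed for eligibility. A baseline SpO2 term for minimal SpO2 may be added but is optional. Leave the logistic model for the binary haemodynamic endpoint as it is.

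The cost is that sentence and a check that the case report form holds these readings. It should be settled before the data are analysed by group, so that the covariate is not chosen after the results are known.
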